## Abstract

**Background:**

Functional constipation (FC) is a common functional gastrointestinal disorder, which brings many negative impacts to the children’s daily life. Pediatric *Tuina* has been proved to be a potential therapy for FC. However, the evidence for its effectiveness and safety is insufficient due to the lack of high-quality study. This study aims to evaluate the efficacy and safety of pediatric *Tuina* for children with FC.

**Methods/design:**

This study is a randomized, controlled, multicentre, clinical trial. We will include 176 children with FC from five hospitals. The participants will be randomly allocated into two groups: the pediatric *Tuina* group and the Medilac-Vita group. This study will include a 1-week actual treatment period and a 2-week follow-up period. Primary outcomes are weekly spontaneous bowel movements and weekly complete spontaneous bowel movements. The secondary outcomes are effective rate, stool form, distress sensation, and glycerine enema rate. The assessment will be performed each week. Adverse event will be monitored in the treatment period and follow-up period.

**Discussion:**

This study is designed to evaluate the efficacy and safety of pediatric *Tuina* for children with FC, and we hypothesize that pediatric *Tuina* is more effective than probiotics. It will provide reliable evidence and support for the treatment of FC by pediatric *Tuina*.

**Trial registration:**

This protocol was registered in the Chinese Clinical Trial Registry (ChiCTR2100046485).

**Supplementary Information:**

The online version contains supplementary material available at 10.1186/s13063-022-06678-y.

## Background

Functional constipation (FC), a common functional gastrointestinal disorder (FGID), which is characterized by infrequent, difficult and incomplete defection [1, 2]. According to the survey report, the prevalence of FC in children ranges from 0.7% to 29.6% (median 12%) [3–5]. Although FC is not life-threatening, it significantly influences the patients’ quality of life and consumes many medical resources [6–8]. Currently, there are two broad categories of treatments for FC: pharmacological and nonpharmacological [9]. Pharmacological treatments have limited therapeutic effects but considerable side effects, while the symptom tends to recur [10–12]. Nonpharmacological treatments, such as physical activity, fiber, and fluid intake, are recommended to regulate bowel movement, whereas the evidence is still insufficient and the strength of recommendation is weak [9, 13, 14]. Therefore, it is urgent to find an effective and safe therapy for FC in children.

Pediatric *Tuina* is a special massage therapy based on traditional Chinese medicine (TCM), which can be traced back to Qin Dynasty (220 B.C.) and the complete system was established in the Ming Dynasty (1601 A.D.) [15]. Up to now, many universities of TCM offer the subjects of pediatric *Tuina* for medicos [16]. The special meridian-acupoint theory is different from adults, most acupoints are located on the finger, palm, and forearm, while few acupoints are located on the head, abdomen, and back [17]. The manipulations such as rubbing, pushing, pinching, kneading, and vibrating are characterized by light, fast, and gentle [18].

In recent years, many randomized controlled trials (RCTs) have indicated that pediatric *Tuina* may be an effective treatment for FC in children [19]. While in other countries, different massage manipulations have also been used for constipation, such as abdominal massage, reflexology, Dalk (Iranian traditional massage), etc. [20–22]. However, the inadequacy of the study design restricts the quality and credibility [19, 22–24]. Well-designed high-quality RCTs are urgently needed.

### Objective

This randomized controlled trial aims to (a) evaluate the efficacy of pediatric *Tuina* for children with FC, (b) evaluate the safety of pediatric *Tuina* for children with FC, and (c) compare the effect of pediatric *Tuina* with Medilac-Vita.

## Methods/design

### Study design

This study is a prospective, randomized, multicentre, controlled design, and it will be conducted from December 2021 to December 2024. We will recruit 176 participants from 5 hospitals in 3 different provinces (Yunnan province, Zhejiang province, and Shandong Province). The eligible participants will be randomly allocated to 2 groups in a 1:1 ratio. The randomization sequence will be computer generated by the Clinical Research Center of the Yunnan University of Chinese Medicine. Every participant will receive a 1-week treatment period and a 2-week follow-up. Basic information and outcomes will be assessed at baseline and after each week. The flowchart is shown in Fig. 1, and the schedule is shown in Table 1.

**Fig. 1 Fig1:**
[figure not shown]
Flowchart of study design

**Table 1 Tab1:** Schedule of the study

Item	Days													
	−7	–	0	1	2	3	4	5	6	7	–	14	–	21
**Eligibility screen**	×													
**Informed consent**	×													
**Baseline**	×	×	×											
**Allocation**			×											
**Pediatric** ***Tuina***			×		×		×		×					
**Medilac-Vita**			×	×	×	×	×	×	×					
**Follow-up**										×	×	×	×	×
**Stool dairy**	×	×	×	×	×	×	×	×	×	×	×	×	×	×
**Assessment**														
**SBMs**			×							×		×		×
**CSBMs**			×							×		×		×
**Effective rate**			×							×		×		×
**m-BSFS**			×							×		×		×
**Distress sensation**			×							×		×		×
**Glycerine enema rate**			×							×		×		×
**Participants safety**														
**Adverse events**			×	×	×	×	×	×	×	×	×	×	×	×

This trial is reported in line with the Standard Protocol Items Recommendations for Interventional Trials (SPIRIT) guidelines, and details are provided in Additional file 1. This trial follows the principles of the Declaration of Helsinki (Version Edinburgh 2000). This protocol was registered in the Chinese Clinical Trial Registry (ChiCTR2100046485) and approved by the Hospital Ethics Committee of Second Affiliated Hospital of Yunnan University of Chinese Medicine (2021–014).

### Participants

This study will include 176 participants from the departments of Acupuncture and *Tuina* in Second Affiliated Hospital of the Yunnan University of Chinese Medicine, Yunnan Province Hospital of TCM, Kunming Children’s Hospital, Zhejiang Provincial People’s Hospital, and Shandong Province Hospital of TCM. The participants will be appropriately compensated after they complete the entire procedure. However, parents or legal guardians of the participants have the right to withdraw from this study at any time, for any reason. And they will not face any discrimination or hardship in the hospital. The participants will be children with FC and they must meet the following eligibility criteria.

### Inclusion criteria

Children aged 1–7 years.Children who meet the diagnostic criteria for functional constipation (Rome IV) [25, 26]. Must include 1 month of at least 2 of the following in infants up to 4 years of age: (1) 2 or fewer defecations per week; (2) history of excessive stool retention; (3) history of painful or hard bowel movements; (4) history of large-diameter stools; and (5) presence of a large fecal mass in the rectum. In toilet-trained children, the following additional criteria may be used: (6) at least 1 episode/week of incontinence after the acquisition of toileting skills and (7) history of large-diameter stools that may obstruct the toilet. For children over 4 years of age, there must include 2 or more of the following occurring at least once per week for a minimum of 1 month with insufficient criteria for a diagnosis of irritable bowel syndrome: (1) 2 or fewer defecations in the toilet per week in a child of a developmental age of at least 4 years; (2) at least 1 episode of fecal incontinence per week; (3) history of retentive posturing or excessive volitional stool retention; (4) history of painful or hard bowel movements; (5) presence of a large fecal mass in the rectum; and (6) history of large diameter stools that can obstruct the toilet.Parents or legal guardians are motivated to participate in the trial.Parents or legal guardians sign written informed consent.

### Exclusion criteria

A history of intestinal surgery.Receiving gastrointestinal prokinetic agent or laxative treatments 14 days before enrollment.Receiving pediatric *Tuina* or probiotics 14 days before enrollment.Children with Hirschsprung’s disease.Children with neurological and psychiatric disorders (e.g., cerebral palsy, autism, spina bifida, anorexia nervosa).Children with any organic or metabolic diseases of hematopoietic, endocrine, or immune systems.

### Drop out criteria

The children’s parents voluntarily asked to withdraw.Patients have a sudden illness during the study.Patients receive other pharmacological or non-pharmacological interventions during the study period.Patients experience severe adverse reactions during the study.The stool diary records are largely missing and incomplete.

### Randomization and blinding

Eligible FC children will be randomly assigned into two groups at a 1:1 ratio, based on the random number. There are two different types of interventions in this study. It is impossible to blind therapists and children’s parents or legal guardians. Nonetheless, outcome assessors and the data analyst will be blinded to the procedure and results of randomization, group allocation, and intervention.

### Sequence generation, allocation and the implementation

The randomization will be conducted by using a computerized random number generator, the Clinical Research Center of the Yunnan University of Chinese Medicine. There will be opaque envelopes with random numbers for random allocation. The envelopes will be managed by an independent member who is not involved in the treatment procedure or data analysis. The opaque envelope will not be opened until the participant is about to receive treatment, and then the participant will be grouped.

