### Sample size

A previous relevant study showed the effective rate of pediatric *Tuina* was 92.5% and Medilac-Vita was 72.5% [35]. Based on our own clinical experience, we consulted pediatric *Tuina* and physician experts. We anticipate an effective rate of 90% in the pediatric *Tuina* group and 70% in the Medilac-Vita group. Considering *α* = 0.05, 1-*β* = 0.90, *p*_1_ = 0.90, *p*_2_ = 0.70, *u*_0.05/2_ = 1.96, *u*_0.1_ = 1.282 [36], $$n=1641.4\times {\left[\frac{\left(1.96+1.282\right)}{\sin \sqrt[-1]{0.90}-\sin \sqrt[-1]{0.70}}\right]}^2$$ = 79.02 ≈ 79. With a drop-out of 10%, 88 FC children will be finally recruited in each group. Totally, 176 participants will be finally recruited in this study.

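### As described, neither the allocation nor the analysis ensures balance across the five hospitals and two age bands; restrict the list if it is not already restricted, and adjust for both factors in either case

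*Protocol article*

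**What the plan says.** Three sections of the protocol article describe allocation.

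- Study design: "The randomization sequence will be computer generated by the Clinical Research Center of the Yunnan University of Chinese Medicine". The same section gives the setting: "We will recruit 176 participants from 5 hospitals in 3 different provinces".
- Randomization and blinding: "Eligible FC children will be randomly assigned into two groups at a 1:1 ratio, based on the random number". Therapists and parents are not blinded.
- Sequence generation, allocation and the implementation: "The randomization will be conducted by using a computerized random number generator", followed by "There will be opaque envelopes with random numbers for random allocation". An independent member holds the envelopes, and each is opened only when the child is about to be treated.

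None of these sections mentions blocks, strata, minimisation or a list per hospital. None calls the randomisation simple or unrestricted either.

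The Sample size section sets the arm size: "With a drop-out of 10%, 88 FC children will be finally recruited in each group". The Statistical analysis section plans an independent-samples t-test or Mann-Whitney test for continuous outcomes, a χ² test for the effective rate, and a subgroup analysis by age below 4 against 4 and over. It plans no term for hospital or age in the comparison of the groups.

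**The concern.** Two factors are built into this trial and are likely to matter.

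**Hospital.** There are five hospitals in three provinces. Outcomes Measurement gives one assessor to the three Yunnan hospitals and one each to the Zhejiang and Shandong hospitals, so province and assessor coincide. The Discussion accepts that manipulation may differ between physicians.

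**Age band.** Age around 4 years sets the Tuina counts (Table 2), the Medilac-Vita amount (Medilac-Vita group section) and the subgroup (Statistical analysis). Primary outcomes says that children older than 4 can answer whether defecation was complete, so age also largely decides who contributes to CSBM, a primary outcome.

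A chance imbalance in either factor can be handled by design, through stratification, or in analysis, through adjustment. As described, the plan does neither. Randomisation still keeps the comparison unbiased on average. What is at stake is precision, the credibility of a single unblinded result with parent-kept diaries, and the balance of the older-child comparison on which CSBM depends.

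**Working it through.** **1. The plan's own figure.** Inputs from Sample size: p₁ = 0.90, p₂ = 0.70, u values 1.96 and 1.282.

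- In degrees, arcsin√0.90 = 71.565 and arcsin√0.70 = 56.789; the difference is 14.776.
- n = 1641.4 × (3.242 / 14.776)² = 79.02, taken as 79.
- 79 / 0.9 = 87.8, so 88 per group and 176 in total.

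The stated 79, 88 and 176 reproduce.

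**2. Arm totals if the list is unrestricted.** The number in one arm is Binomial(176, 0.5).

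| Event | Probability |
|---|---|
| Exactly 88:88 | 6.0% |
| An arm 5 or more away from 88 | 49.8% |
| An arm 10 or more away from 88 | 15.2% |

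The 95% range for one arm is 75 to 101.

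**3. What unequal totals cost in power.** On the plan's arcsine scale, h = 2(arcsin√0.90 − arcsin√0.70) = 0.5158 radians, and power = Φ(h·√(n₁n₂/(n₁+n₂)) − 1.96). With 10% dropout in each arm:

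| Randomised | √(n₁n₂/(n₁+n₂)) | Power |
|---|---|---|
| 88:88 | 6.293 | 90.1% |
| 78:98 | 6.252 | 89.7% |
| 75:101 | 6.224 | 89.4% |

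The loss at the edge of the 95% range is 90.1 − 89.4 = 0.7 points.

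**4. Hospitals, if unrestricted.** Hospital sizes are not given. Assume four of 35 and one of 36 (4 × 35 + 36 = 176).

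- Hospital of 35: one arm ranges from 12 to 23 (95%). A gap of 10 or more means 12 or fewer in the smaller arm: 2 × P(X ≤ 12) = 0.0895. A 60:40 split or worse (14 or fewer) has probability 31%.
- Hospital of 36: a gap of 10 or more means 13 or fewer: 2 × P(X ≤ 13) = 0.1325.
- At least one of five: 1 − (1 − 0.0895)⁴ × (1 − 0.1325) = 0.404, about 40%.

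**5. Age band, if unrestricted.** The age mix is not given. Assume 88 children aged 4 or over.

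- One arm ranges from 35 to 53 of the 88 (95%).
- A gap of 10 or more (39:49 or worse) has probability 2 × P(X ≤ 39) = 33.7%. If the number aged 4 or over is itself random around half, this is about 31%.
- Efficiency relative to 44:44 is 4n₁n₂/88². It is 98.7% at 39:49 and 95.8% at 35:53.

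**6. What restriction would achieve.** Simulated permuted blocks, with strata of equal expected size (assumption):

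| Scheme | 95% range, one arm | Exactly 88:88 | Largest gap within a stratum |
|---|---|---|---|
| 10 strata (hospital × age), blocks of 4 | 85 to 91 | 28% | 2 |
| 10 strata, blocks of 4 and 6 | 85 to 91 | 25% | 3 |
| 5 strata (hospital), blocks of 4 and 6 | 86 to 90 | 34% | 3 |

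In the ten-stratum schemes the largest gap seen within a hospital was 4 (blocks of 4) or 6 (blocks of 4 and 6).

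**The case against.** The strongest objection is that the concern argues from silence. The article does not say that the list is unrestricted. A blocked list, a list fixed at 88:88 or one list per hospital would fit the same words, and an article may leave block details to the full protocol. This stands: every probability in steps 2, 4 and 5 is conditional. It does not reach the analysis, because the between-group tests are named and have no hospital or age term. If the list does turn out to be stratified, tests that ignore the strata waste part of the benefit.

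Second, imbalance is not the same as harm. Unequal totals cost under 1 point of power, a 39:49 split among the older children keeps 98.7% of the efficiency, and randomisation guards against systematic bias. This also stands. The documents give no prognostic effect of hospital or age, so the precision lost through imbalance, or regained by adjustment, cannot be put in figures.

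Third, stratifying by hospital cannot even out differences between Tuina therapists across the arms, because only one arm receives Tuina. Assessor balance needs three strata, not five. Both points are fair. Hospital remains a sensible factor because it may carry differences in case mix and local practice, but those reasons should not be overstated.

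Fourth, small blocks in ten strata averaging 176/10 = 17.6 children, with unblinded therapists, make some allocations guessable. This is a real trade-off. It favours varying, concealed block sizes, and it leaves hospital-only strata as a reasonable choice.

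**Conclusion.** The concern holds in a limited form. As described, neither the allocation nor the analysis ensures balance over hospital or age band. If the list is unrestricted, one arm ranges from 75 to 101 of 176. With about 35 children per hospital, there is about a 40% chance of a gap of 10 or more in at least one hospital. With half the children aged 4 or over, there is about a 31 to 34% chance of such a gap among them. The equal hospital sizes and the half share are assumptions.

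Four stronger readings are tempting, and the documents do not support them:

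- *The trial uses simple randomisation and so will miss 88 per group.* The type is not stated, and 88 is a target from the power calculation.
- *Stratified blocks would deliver 88:88.* They do so exactly in only about 25 to 28% of runs with ten strata; they narrow the range to about 85 to 91.
- *The trial loses meaningful power.* The loss from arm totals is under 1 point.
- *Recruitment has certainly not begun.* Trial status places the trial in therapist training, and the Discussion puts that training before the study starts, so this is a fair inference. It is not a statement, and Study design plans a start in December 2021.

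The change is worth making because it is cheap, needs no extra children and concerns factors already recorded. It corrects no validity failure.

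**What to change.** 1. **State the type of randomisation.** If the list is already restricted, one sentence giving the method and strata settles the design part.
2. **If it is unrestricted and the sponsor confirms that enrolment has not begun,** have the same centre generate a new list in permuted blocks of randomly varying size (for example 4 and 6), concealed from the sites, stratified by hospital and, if practicable, by age band (<4, ≥4). Expect an overall arm of about 85 to 91 and gaps of at most 2 to 3 within a stratum, not exactly 88:88.
3. **In either case, replace the unadjusted between-group comparisons** with models containing treatment, hospital and age band: a linear or other suitable regression for the bowel-movement and scale outcomes, and a logistic model for the effective rate. Where CSBM is analysed only in the older children, hospital alone is needed.

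Cost: a new list, five or ten envelope series in place of one, and a revised analysis paragraph. The downside is some predictability at block ends in an open-label trial. Varying block sizes reduce it but do not remove it, and hospital-only strata halve the number of series. If enrolment has begun, step 3 still applies.

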### Interventions

To ensure all manipulations follow the standard procedures. The therapists in this trial own an official medical license and hold a master’s degree in pediatric *Tuina*. During this period, participants are not allowed to use any other interventions, at least in principle. If participants take any other interventions in this period, they will be defined as non-adherent and will be dealt with drop out.

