#### Stool diary

Parents or legal guardians are required to keep a stool diary from baseline to intervention period and follow-up period. The stool diary contains 5 domains: weekly spontaneous bowel movements (SBMs), weekly complete spontaneous bowel movements (CSBMs), stool form, distress sensation, and glycerine enema rate.

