#### Secondary outcomes

The secondary outcomes are effective rate, stool form, distress sensation, and glycerine enema rate. The effective rate is the number of participants who are effective (on average, at least one bowel movement in 3 days, stool softening, defecate unobstructed) divided by a total number of the group. Stool form will be measured according to the modified Bristol stool form scale (m-BSFS) (Table 3), which classifies the form of children’s feces into 5 types from separate hard lumps (type 1) to entirely watery (type 5) [33, 34]. Distress sensation measured in the range of 0–3 represents the intensity of distress during defecation, “0” means no cry or grimace, “1” means slight cry and grimace, “2” means medium cry and grimace, and “3” means hysterical cry and grimace. Glycerine enema rate is the times of using glycerine enema divided by the times of defecation, within a week.

**Table 3 Tab3:** Modified Bristol stool form

**Type**	1	2	3	4	5

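### The drop-out rule for other interventions does not exempt glycerine enema, although the enema rate is a secondary outcome measured after randomisation

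*Protocol article*

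**What the plan says.** Two groups of statements in the protocol article bear on the same event, a child being given a glycerine enema after randomisation.

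**Rules on other treatment.**
- Interventions: "participants are not allowed to use any other interventions, at least in principle". The next sentence gives the consequence: "If participants take any other interventions in this period, they will be defined as non-adherent and will be dealt with drop out".
- Drop out criteria: one listed criterion is "Patients receive other pharmacological or non-pharmacological interventions during the study period".
- Neither section names an exemption, and no other section lists glycerine enema as permitted rescue.

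**Rules on measuring enema use.**
- Table 1 has an assessment row "Glycerine enema rate", marked at days 0, 7, 14 and 21.
- Stool diary: the five domains are weekly SBMs and then "weekly complete spontaneous bowel movements (CSBMs), stool form, distress sensation, and glycerine enema rate".
- Secondary outcomes: "Glycerine enema rate is the times of using glycerine enema divided by the times of defecation, within a week".
- Discussion: enema is described as the usual aid when stool is lumpy and defecation difficult, and its rate as a sign of whether the child can defecate unaided.

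**The concern.** A glycerine enema is an intervention other than the two study treatments, so the general rule turns its use into drop-out. The outcome section treats the same use as data to be collected in each of the three weeks after randomisation. A site cannot follow both.

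Three things are at stake if the drop-out rule is applied as written:

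- **The enema outcome.** The children it is meant to describe are the ones removed.
- **The primary outcomes.** A child dropped in week 1 may contribute no SBM or CSBM data at days 14 and 21. The loss is tied to poor response, so it is informative, and it would be expected to be larger in the arm with more failures. The Statistical analysis section allows expectation maximization, last observation carried forward or listwise deletion for missing data. Listwise deletion would remove these children entirely.
- **Consistency.** Five hospitals and three assessors have to apply the rule. Some could drop enema users while others keep them.

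**Working it through.** **1. Does any wording remove the conflict?**

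- The qualifier in "participants are not allowed to use any other interventions, at least in principle" softens the ban. The drop-out sentence that follows carries no qualifier, and neither does the criterion under Drop out criteria.
- The Interventions section speaks of a period that could mean only the treatment week. The Drop out criteria refer to the study period, so the assessments at days 14 and 21 are covered too.
- Measuring the enema rate implies that use is tolerated, but this is an inference. No sentence says so.

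The conflict therefore stands on the text.

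**2. What happens to the enema outcome under the literal rule?**

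The outcome is enema uses divided by defecations in a week. A child who stays in has used no enema since baseline, so the numerator is 0 and the rate is 0 at days 7, 14 and 21 in both arms. A non-zero value could come only from a child already classed as a drop-out, and only if the week of use were still counted. The article does not say whether it would be.

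**3. The planned sample size, reproduced.**

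Inputs from Sample size: p1 = 0.90, p2 = 0.70, two-sided alpha 0.05, power 0.90, drop-out 10%.

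- asin√0.90 = 71.565° and asin√0.70 = 56.789°, a difference of 14.776°.
- n = 1641.4 × (3.242 / 14.776)² = 79.02, taken as 79 per group.
- 79 / 0.90 = 87.8, so 88 per group and 176 in total.

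This agrees with the article. Exempting enema does not change it.

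**4. Illustration for the effective rate.**

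The documents give no enema frequency. Let s be the share of non-responders who use an enema, assumed equal in both arms and taken from 10% to 50%. Assume also that users leave the denominator, that only non-responders use enemas, and that there is no other drop-out. Non-responders are 10% (Tuina) and 30% (Medilac-Vita), so

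p1 = 0.90 / (1 − 0.10s), p2 = 0.70 / (1 − 0.30s), with 88 × 0.10s and 88 × 0.30s children removed.

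| s | Tuina vs Medilac-Vita | Difference (points) | Removed per arm | Total removed | Arcsine power |
|---|---|---|---|---|---|
| 10% | 90.9% vs 72.2% | 18.7 | 0.9 vs 2.6 | 3.5 | 0.906 |
| 25% | 92.3% vs 75.7% | 16.6 | 2.2 vs 6.6 | 8.8 | 0.859 |
| 50% | 94.7% vs 82.4% | 12.4 | 4.4 vs 13.2 | 17.6 | 0.719 |

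For reference, power is 0.900 with 79 per arm at 90% versus 70%, and 0.928 with 88 per arm and no removals. It passes below 0.90 between s = 12% (0.901) and s = 13% (0.898). At s = 50% the removals equal the whole drop-out allowance (10% of 176 = 17.6).

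**5. The other reading of the denominator.**

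The effective rate is the number of effective children "divided by a total number of the group". If drop-outs stay in that total as non-effective, the removed non-responders count exactly as they would have anyway, and 90% versus 70% is unchanged. This is the more natural reading, so the table in step 4 shows what could happen and is not a forecast.

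**The case against.** The strongest reply is that the document, read as a whole, is clear enough. A measure that is a diary domain, has a weekly definition, is scheduled after treatment and has a stated rationale cannot also be forbidden. On that view other interventions means competing treatments, and the enema is a recorded aid. As to intent, this is probably right, and nothing suggests that the sponsor chose to drop enema users. It does not repair the text: the drop-out rule covers pharmacological and non-pharmacological measures without exception, and follow-up lost under it cannot be recovered at analysis. Nor is this a detail that an article may leave to the full protocol, because two stated rules collide.

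It can also be said that the harm depends on unstated steps: that sites take the rule literally, that drop-out ends data collection, and that dropped children leave the denominator. That stands as a limit on size. Expectation maximization and last observation carried forward are allowed alongside listwise deletion, and the documents do not say what happens to the week in which an enema was used.

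Stronger readings are tempting, and the documents do not support them:

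- *The trial is underpowered.* The power figures rest on an assumed enema share and on removal from a denominator defined as the group total. They also concern the effective rate, which is a secondary outcome although the sample size is built on it.
- *The rule favours Tuina.* With an equal share of users among non-responders, the contrast shrinks.
- *Enema-assisted stools inflate the effective rate.* A reader might infer this because the definition is "on average, at least one bowel movement in 3 days, stool softening, defecate unobstructed" and does not say spontaneous. Its last component would ordinarily fail a child who needs an enema.

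**Conclusion.** The point holds as a conflict between stated rules, and it should be fixed. Two consequences follow from the literal wording without any assumed enema frequency: the enema rate among retained children is zero after baseline, so it cannot compare the arms, and drop-out is triggered by poor outcome. Loss of later SBM and CSBM data is a risk, not a certainty, because it depends on whether sites stop collecting data after drop-out.

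No size can be put on the effect from the documents. For the effective rate it runs from none, if drop-outs are kept as non-effective, to the illustrative losses tabulated above. Those need the assumed 10% to 50% share and removal from the denominator, and even then there is no loss against the planned 0.90 at a 10% share. The sample size itself is not in error on this point.

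**What to change.** In both Drop out criteria and Interventions, add a clause that glycerine enema is permitted rescue, is recorded in the stool diary and is not a drop-out event. Add one sentence that children who use it continue follow-up and are analysed in their allocated group. That sentence is an analysis rule and can sit in the Statistical analysis section or the analysis plan. The clause in the two trial-conduct sections cannot wait for the analysis plan, because sites act on it.

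Keep the enema rate as the defined weekly ratio. Leave the definition of effective unchanged: restricting it to spontaneous movements would redefine the endpoint behind the 90% and 70% assumptions.

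The cost is a clause in two places and one analysis sentence. The diary already captures enema use, so no new data are needed, and 79, 88 and 176 stand. Trial status reports that therapists are still being trained, so on that account the wording can be settled before enrolment.
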